#### Participant assessments

Women who have provided consent are asked to complete a baseline assessment prior to receiving the intervention. This assessment consists of a series of self-report and interviewer administered questionnaires regarding health, mental health, social service involvement, and substance use. These constructs were selected for assessment given that the interventions and services provided to participants were anticipated to have an impact on these areas. Two follow-up assessments are collected: a pre-delivery follow-up at 34 to 40 weeks of gestation and a post-delivery follow-up 30 days following delivery. These assessments contain the same questionnaires as the baseline assessment, with the exception of the Adverse Childhood Experience scale since these scores are related to childhood experiences and therefore should not vary over the course of the study. We are also collecting data from the woman’s and her infant’s medical records (Table 4). In addition, our team will work with the local department of health to obtain county level data across time at the conclusion of the project to assess intervention impact within the larger community (Table 4). In the event that a participant chooses to discontinue their participation in the study, no additional data will be collected from that participant.

**Table 4 Tab4:** Patient-level study measures

Source	Outcome	Domain	Instrument	Source of data	Baseline	Pre-delivery follow-up	Post-delivery follow-up
Health department	Hepatitis B Virus (HBV)	Health	ICD10 Code B16	Health department	X		X
	Hepatitis C Virus (HCV)	Health	ICD10 Code B18.2	Health department	X		X
	Human Immunodeficiency Virus (HIV)	Health	ICD10 Code B20	Health department	X		X
	Syphilis	Health	ICD10 Code A53.9	Health department	X		X
	Gonorrhea	Health	ICD10 Code A54.9	Health department	X		X
	Chlamydia	Health	ICD10 Code A74.9	Health department	X		X
	Child welfare involvement	Social	ICD10 Code Z62.21	Health department	X		X
	Overdose	Health	ICD10 Cod T40.6	Health department	X		X
Medical record	Pre-eclampsia	Health	ICD10 Code O14	Medical record			X
	Pre-term birth	Health	ICD10 Code O60	Medical record			X
	Cesarean section	Health	ICD10 Code O82;	Medical record			X
	Intrauterine growth restriction	Health	ICD10 Code P05.9	Medical record			X
	Birth weight	Health	ICD10 Code P07	Medical record			X
	Apgar score	Health	ICD10 Code P09	Medical record			X
	Neonatal opioid withdrawal syndrome (NOWS) severity	Health	ICD10 Code P96.1	Medical record			X
	Length of hospital stay	Health	Discharge dates	Medical record			X
	Continuity of MOUD	QI	Prescriptions Filled	Medical record			X
	Illicit drug use	SUD	Urinalysis	Medical record	X	X	X
	Number of infant ER visits	Health	CPT 99,281–99,285	Medical record			X
	Adequacy of prenatal care	QI	Adequacy of Prenatal Care Utilization (APNCU)	Calculated from medical record			X
Medical record/self-report	Overdose events	SUD	ICD10 Code T40.2X1A	Medical record/Self-report	X		X
Self-report	Overall health	All	12-Item Short Form Survey (SF-12)	Self-report	X	X	X
	Substance misuse	SUD	Adapted Drug Abuse Screening Test (DAST)	Self-report	X	X	X
	Trauma history	Social	Adverse Childhood Experience (ACE)	Self-report	X		
	Alcohol misuse	SUD	Alcohol Use Disorders Identification-Concise (AUDIT-C)	Self-report	X	X	X
	OUD	SUD	Diagnostic and Statistical Manual 5 (DSM-5) Opioid Use Disorder (OUD) Checklist	Self-report	X	X	X
	Depression	Mental Health	Edinburgh Postnatal Depression Scale (EPDS), Patient Health Questionnaire-9 (PHQ-9)	Self-report	X	X	X
	Nicotine dependence	SUD	Fagerstrom Test for Nicotine Dependence (FTND)	Self-report	X	X	X
	Anxiety	Mental health	Generalized Anxiety Disorder-7 (GAD-7)	Self-report	X	X	X
	Psychological distress	Mental health	Kessler Psychological Distress Scale (K6)	Self-report	X	X	X
	Parental knowledge & skills	Social	Parenting and Family Adjustment Scale (PAFAS)	Self-report	X		X
	Patient satisfaction	QI	Patient Satisfaction Questionnaire Short Form (PSQ-18)	Self-report		X	X
	Patient utilization of services	QI	Treatment Services Review-6 (TSR-6)	Self-report	X	X	X
	Post-traumatic stress disorder (PTSD)	Mental health	Primary Care PTSD Screen for DSM-5 (PC-PTSD-5)	Self-report	X	X	X

*QI* quality improvement, *SUD* Substance Use Disorder, *IC10* International Classification of Disease, 10th Revision, *CPT* Current Procedural Terminology

Our team chose several reliable and valid self-report instruments to assess substance use at the patient-level. The Alcohol Use Disorders Identification-Concise (AUDIT-C) is a measure of unhealthy alcohol use [40]. The Diagnostic and Statistical Manual 5 (DSM-5) OUD Checklist is an instrument to assess OUD [41]. The Fagerstrom Test for Nicotine Dependence (FTND) captures the presence of nicotine dependence [42]. Finally, we adapted the Drug Abuse Screening Test (DAST) [43] to assess opioid-specific participant behaviors.

To assess mental health, patients complete the Edinburgh Postnatal Depression Scale (EPDS), a 10-item scale for detection of postnatal depression, [44] as well as the Patient Health Questionnaire-9 (PHQ-9) [45]. Participants also complete the Generalized Anxiety Disorder-7 (GAD-7) to assess anxiety, [46] and the Kessler Psychological Distress Scale (K6) to capture psychological distress [47]. We also administer the 12-Item Short Form Survey (SF12) to assess overall well-being and health functioning [48]. Participants likewise complete the Adverse Childhood Experience (ACE) questionnaire, [49] a 10-item instrument inquiring about the presence of childhood abuse and household dysfunction, as well as the 5-item Primary Care PTSD Screen for DSM-5 (PC-PTSD-5) [50] for detecting the presence of post-traumatic stress disorder (PTSD) in a healthcare setting. We also utilize the 30-item Parenting and Family Adjustment Scale (PAFAS) [51] to assesses parenting practices and family relationships.

Lastly, our team also assesses participant satisfaction with the nurse care manager intervention and utilization of services. To assess this area, we administer the Patient Satisfaction Questionnaire Short Form (PSQ-18) [52] and the Treatment Services Review-6 (TSR-6) which captures utilization of healthcare services such as care management [53]. Additionally, we utilize a care management output form, which captures the frequency and type of patient outreach completed by the nurse care manager weekly, including number of calls, texts, greeting cards, accompanied appointments, linkage to psychosocial support, and referrals to medical provider.

Outcomes for women and neonates obtained from medical record assessments include pre-eclampsia, pre-term birth, cesarean section, intrauterine growth restriction, birth weight, Apgar score, NOWS severity, maternal and infant length of hospital stay, continuity of MOUD, illicit drug use, number of infant ER visits, and the Adequacy of Prenatal Care Utilization (APNCU) index is calculated to measure resource utilization [48]. NOWS severity will be assessed using the modified Finnegan Neonatal Abstinence Scoring System, [54] as this is the method utilized by the local hospital that serves the target counties. Data to be collected from local health officials at the conclusion of the study will include county-level prevalence of hepatitis B virus, hepatitis C virus, human immunodeficiency virus (HIV), gonorrhea, chlamydia, number of overdoses, and child welfare involvement.

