## Methods

### Design

This two-year study is employing a one group, repeated measures, hybrid type-1 effectiveness-implementation design, [28] which emphasizes clinical effectiveness monitoring while also gathering information regarding the implementation of the program. This study delivers interventions at 2 levels, both targeting improvement of care for pregnant women with OUD. The first area of focus is at the *community healthcare provider-level*, which aims to evaluate the acceptability and feasibility of perinatal OUD education across time and to improve provider education by increasing knowledge specific to: MOUD provision; screening, brief intervention, and referral to treatment (SBIRT) utilization; and NOWS treatment. The second area of intervention focus is at the *patient-level*, which assesses the preliminary effect of perinatal OUD provider education in promoting illicit opioid abstinence and treatment engagement among pregnant women with OUD. The research team is interested in assessing changes across time among recipients. Time and resources necessary to implement an experimental or quasi-experimental design are not available for this project. For this reason, the research team has chosen to utilize a single arm design. The University of Utah Institutional Review Board approved this study.

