### Study setting

The study setting for this project is rural Utah. From 1999–2014, the proportion of women with OUD delivering at a hospital in Utah has increased nearly ten-fold [1]. Utah ranks among the highest nationally in terms of opioid overdose rates among women [29] and frequency of opioid prescribing to pregnant women insured by Medicaid (41.6%) [30]. The leading cause of deaths among pregnant and postpartum women in this state is drug-related, with 77% of these deaths involving opioids [3].

Two adjacent rural counties [31] in Utah were chosen as the target for the intervention, with a local women’s health clinic as the focal point of care. These counties were selected because of the high rates of opioid overdose, limited resources, and high degree of existing community engagement [32–34]. These two rural counties lead the state in rates of opioid overdose deaths, with collectively 47.7 per 100,000 compared to the state average of 17.4 deaths per 100,000 [32].

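### County-level data are meant to show intervention impact, but no comparison series is named and the two counties were chosen partly for high overdose rates

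*Protocol article*

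**What the plan says.** In the protocol article, Participant assessments states that the team will work with the local health department to "obtain county level data across time at the conclusion of the project to assess intervention impact within the larger community". The same section adds: "Data to be collected from local health officials at the conclusion of the study will include county-level prevalence of" several infections, and it also lists the number of overdoses and child welfare involvement. Table 4 gives the health department as the source for these measures.

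Study setting explains the choice of counties: "These counties were selected because of the high rates of opioid overdose, limited resources, and high degree of existing community engagement". It then reports that the pair rank highest in Utah on opioid overdose mortality, giving the figures as "collectively 47.7 per 100,000 compared to the state average of 17.4 deaths per 100,000".

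Design explains the single arm: "Time and resources necessary to implement an experimental or quasi-experimental design are not available for this project". Limitations acknowledges that there is no control group and points to evaluation through RE-AIM. The t-tests and chi-square tests under Analyses are described for participant outcomes. The article names no comparison county, state series or pre-intervention trend for the county data.

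**The concern.** The county data carry a causal purpose, and the article names nothing to compare them with. Three things follow.

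- **Regression to the mean.** When units are picked partly because a noisy rate is high, later values of that rate, or of one close to it, tend to be lower even if nothing has changed. Here the rate behind the selection is overdose deaths and the county outcome is number of overdoses.
- **Secular trend.** Overdose, infection and child-welfare figures move for reasons unrelated to the programme. Without a benchmark, that movement cannot be separated from an effect.
- **Dilution.** The county figures cover the whole population, while the patient-level intervention serves pregnant women with OUD. A real effect in that group would be a small part of the county total.

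If the stated purpose is followed, background change could be credited to the programme, or a real effect could be hidden. The findings go to a final report to the state and are offered as evidence for models of care, so the reading of the county data matters.

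**Working it through.** The article states no county-level calculation, so there is no figure to reproduce. The steps below show what the stated rates allow and where assumptions begin.

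**Inputs from the article (Study setting):** county rate 47.7 and state average 17.4 deaths per 100,000. Ratio: 47.7 / 17.4 = 2.74. This shows how extreme the counties were; it does not measure regression to the mean.

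**Inputs the article does not give, taken as assumptions:** combined population 10,000 to 50,000; 1 to 5 years of data behind the 47.7; coefficient of variation (CV) of true rates between counties 0.3 to 0.8.

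**1. Regression to the mean (gamma-Poisson shrinkage toward the state mean).** Let a = 1/CV², b = a/0.000174, n = population × years and d = 0.000477 × n. The expected later rate with no effect is (a + d)/(b + n).

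Example with 30,000 people, 3 years and CV 0.5: a = 4, b = 22,989, n = 90,000, d = 42.9. Expected rate = 46.9/112,989 = 41.5 per 100,000, a fall of 13%.

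| Population | Years behind 47.7 | CV | Expected rate per 100,000 | Fall with no effect |
|---|---|---|---|---|
| 10,000 | 1 | 0.3 | 21.5 | 55% |
| 30,000 | 1 | 0.5 | 34.6 | 28% |
| 30,000 | 3 | 0.5 | 41.5 | 13% |
| 30,000 | 5 | 0.5 | 43.7 | 8% |
| 50,000 | 5 | 0.8 | 46.6 | 2% |

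The result depends almost wholly on inputs the article does not give. The table applies to death rates and assumes that the before period is the one that produced the 47.7. A before period later than the selection years would show less of this.

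**2. Secular trend.** Take 30,000 people, two years before and two after, with no effect. Expected deaths before: 0.000477 × 30,000 × 2 = 28.6. A 10% yearly background decline over two years multiplies this by 0.9² = 0.81, giving 23.2. By simulation, the later count is then lower about 75% of the time, against 47% with no trend. A 10% yearly rise would multiply it by 1.1² = 1.21 and push the other way. The trends quoted in Background and Study setting are rising; for example, OUD at delivery in Utah rose nearly ten-fold from 1999 to 2014.

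**3. Imprecision, which is separate from bias.** With 30,000 people and one year (about 14 deaths), the exact 95% Poisson interval around 47.7 is 26.3 to 79.6 per 100,000. With three years it is 34.5 to 64.3. If non-fatal overdoses are counted, the numbers would be larger and the intervals relatively narrower.

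**The case against.** The best reply has four parts.

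- **The missing control is disclosed.** Design gives time and resources as the reason, Limitations repeats it, and the study is called a pilot. This stands as a description of the trial. It does not cover the county data, because the impact purpose is kept and RE-AIM supplies no counterfactual.
- **A benchmarked comparison is itself quasi-experimental, which the team ruled out.** This is partly fair. However, the proposal needs only aggregate records, with no enrolment or patient contact, and the article already quotes a state rate. If even that is too much, a change of wording is enough.
- **The county analysis is not specified, and the full protocol may say more.** This stands in part. A reader might infer a fixed two-point before-after test, but the wording is compatible with a multi-year series, and the marks in Table 4 sit in participant-visit columns rather than calendar periods. The point therefore rests on the stated impact purpose, not on an assumed test.
- **Selection on overdose is only part of the story.** This stands. High overdose rates were one of three reasons, and deaths are not the same measure as number of overdoses. A reader might infer that falls in infections or child-welfare cases are also expected from selection. The documents do not support that, because those measures were not selection criteria.

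**Conclusion.** The point holds in a limited form. The article gives uncontrolled county data an impact purpose in two counties chosen partly for high overdose rates, with overdoses among the outcomes. Regression to the mean could lower the overdose figure with no effect. Its direction is clear for that outcome; its size is not. The illustrative 2% to 55% rests on assumed population, years and between-county variation, and it could be negligible if the quoted rate pools many years.

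A reader might go further and conclude that the bias as a whole favours the programme. The documents do not support that: trend can act either way, the cited trends are rising and could mask a benefit, chance is symmetric, and dilution pulls toward no visible effect.

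The county data are an addition to the provider and patient measures, so the main aims are unaffected. The change is still worth making, because it is cheap and the data are requested only when the project ends.

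**What to change.** Ask the health department for the same annual aggregate series for the state and the other rural Utah counties as well as the two study counties, covering several years before kick-off and the study years. Report the two counties' change relative to the change elsewhere, with Poisson intervals.

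The two parts do different work. The comparison series deals with shared trend. The longer pre-kick-off period deals with regression to the mean, which an unselected benchmark does not remove: at 30,000 people and CV 0.5, the expected fall drops from 28% when the high rate comes from one year to 8% when it is a five-year average. State the years and population behind the 47.7 as well.

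If this is not done, describe the county data as context and delete the impact purpose from Participant assessments.

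Cost: a slightly larger aggregate request, one extra analysis or a change of wording, and no patient contact. The estimate will be wider and may be less favourable, and dilution will remain.

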To what extent did perinatal addiction education reach the pregnant women with OUD within the healthcare system in Your Counties?	Local healthcare and social service agencies	Electronic medical records; health department records	Number of patient participants/ total number of pregnant women with opioid misuse in Your Counties during the study duration
Efficacy			
How effective was the provider training and support?	Community providers	Questionnaires assessing skills, knowledge and satisfaction	Mixed method surveys regarding provider experience and skillset
How effective were perinatal addiction education services in improving care for pregnant women with OUD?	Healthcare and social service records; patient participants	Compare data regarding illicit substance use, MOUD continuity, opioid poisoning occurrences, physical and mental health, and social service involvement; questionnaires to assess patient perception	Medical codes; standardized comprehensive wellness measurement instruments; qualitative surveys
Adoption			
To what extent are community providers using perinatal addiction education practices when treating patients with perinatal OUD?	Community providers; local healthcare agencies	Questionnaires assessing provider practices and attitudes; electronic medical records	Mixed methods surveys regarding provider practices; frequency of MOUD provision, NOWS treatment and SBIRT by participating community providers
To what extent are patients utilizing resources made available through the perinatal addiction education program?	Partnering agencies (e.g. EUWH, Four Corners Behavioral Health); medical records; pharmacy records	Interviews with partner agencies; electronic medical record and pharmacy record evaluation	Utilization of care management and resources made available through this project; number of MOUD prescriptions filled; presence of BUP in urinalysis via medical record
Implementation			
What were the barriers and facilitators of high quality care?	Community providers	Questionnaires and focus groups	Perceptions of and feedback regarding the implementation kickoff event, as well as ongoing training and support provided via the implementation of perinatal addiction education
Maintenance			

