### Analyses

Following study conclusion, we will employ descriptive statistics to calculate measures of central tendency, frequencies, and proportions for patient demographics and substance use, health, social, and mother/child indicators.* T*-tests and* χ*^2^ tests will be used to assess mean and proportional differences in both cross-sectional and changes in repeated measures across study time points for participant outcomes. As this is a pilot study, powered analyses are not the purpose of this project and thus we do not have a target number of participants for enrollment [55]. The research team will not be conducting subgroup or interim analyses.

Qualitative data collected during the community needs assessment will be analyzed using the procedure for Rapid Identification of Themes from Audio Recordings (RITA) described by Neal and colleagues [56]. Though the inclusion of qualitative data can greatly enrich quantitative data, the slow and labor-intensive process of analyzing it can be a barrier due to time constraints [57, 58]. The RITA approach was developed as way to increase the speed of the analysis process while preserving more of the original data. It is applied to the actual audio recordings of semi-structured interviews. The process involves several time-saving steps to improve efficiency of qualitative data analysis. These include pinpointing research foci for which RITA will be used, creating a codebook of key themes identified and their valence (positive, neutral, or negative context), creating a coding form, refining the codebook, coding, and analyzing codes. A key time-saving feature of RITA is that during analysis, audio recordings are broken down into shorter time segments. The coding form is a grid listing themes and time segments, and coders mark the themes present in each time segment [56].

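### Table 4 gives overdose two different, non-overlapping ICD-10 codes without explanation; applied as printed, each would retrieve only part of the outcome the text states

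*Protocol article*

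**What the plan says.** Table 4, in the Participant assessments section of the protocol article, has two overdose rows, both marked for baseline and post-delivery.

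- The row Overdose has the health department as its only source. Its instrument cell reads "ICD10 Cod T40.6".
- The row Overdose events has the source "Medical record/self-report". Its instrument cell reads "ICD10 Code T40.2X1A".

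The text of the same section says what the health-department data are for: the team will "obtain county level data across time at the conclusion of the project to assess intervention impact within the larger community". It lists the county items to be collected, ending with "number of overdoses, and child welfare involvement". Under Efficacy, Table 2 (Implementation framework) describes the comparison as "Compare data regarding illicit substance use, MOUD continuity, opioid poisoning occurrences, physical and mental health, and social service involvement". The Analyses section plans t-tests and chi-squared tests that include "changes in repeated measures across study time points for participant outcomes".

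The article does not explain why the two codes differ, give a wider code list, or restrict overdose to one substance group or one intent.

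**The concern.** An instrument cell that names a code tells the person who runs the extract what to search for. Here it says two different things for what the plan presents as the same kind of event, and both are narrower than the outcome as worded elsewhere.

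If the cells are followed literally, each series would count a subset of overdoses, and a different subset in each. This matters most for the county series. It is meant to show whether the programme had an effect beyond the enrolled women, and the two counties were chosen partly for their high overdose rates (Study setting). A team replicating the protocol, which the article invites, would inherit the same two codes.

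**Working it through.** The plan states no figure for this outcome, so there is nothing to reproduce. The check sets the entries side by side.

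1. **County row.** Code T40.6, a whole subcategory. Source: health department only.
2. **Participant row.** Code T40.2X1A. The string shows that it lies under T40.2 and is extended to a single full code, so it is narrower than T40.2 itself. Source: medical record or self-report.
3. **Overlap.** T40.2 and T40.6 are sibling subcategories of T40. A search on one does not return an event recorded only under the other. The rows therefore differ in the group of codes they cover and in breadth (a whole subcategory against one full code).
4. **Against the stated outcome.** The plan labels events under either code as overdose. Each code alone therefore leaves out events that the plan itself calls overdose. The wording in the county-data text is not limited by drug or intent, and the wording in Table 2 is limited to opioids but to no opioid class or intent. Both are wider than either cell. This step needs only the plan's own labels and the code strings, not the code descriptions.
5. **What is lost if the cells are applied as printed.** Let p be the share of county overdoses coded T40.6. The county count misses 1 − p. Let q be the share of participants' overdoses coded T40.2X1A, and s the share of the remainder that self-report recovers. The participant count misses (1 − q)(1 − s). The documents give none of p, q or s, so each missed share could lie anywhere from 0% (p = 1; q = 1 or s = 1) to 100% (p = 0; q = 0 and s = 0).
6. **Effect of a common set.** A set containing all of T40.2 and T40.6 returns every event that either printed code returns. On the same records it can never miss more than either code alone.

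**The case against.** The strongest reply is that the cells were never meant as exhaustive definitions. The instrument column is loose elsewhere. Birth weight is paired with P07 and Apgar score with P09, yet one diagnosis code cannot record a weight or a score, and the text names no substitute measure for either. For withdrawal severity the table prints P96.1, while the text says "NOWS severity will be assessed using the modified Finnegan Neonatal Abstinence Scoring System". On this reading the text states the overdose outcome and the table offers an example code. A condensed article may also leave the full extraction list to the protocol version it cites, which is not shown. This part of the reply stands: the overdose codes cannot be shown to be binding. It does not remove the discrepancy. Two different example codes for one outcome still mislead an extractor, and for overdose the article offers no other operational definition.

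Further points also stand. The rows cover different levels and sources, so having two rows is not an error, and no stated analysis compares one with the other. A code held fixed still allows comparison over time within each series. Self-report is not limited by any code, so an under-count among participants is not established. The study is a pilot without powered analyses, and no sample size rests on this outcome.

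A reader might also infer that, because the codes are mutually exclusive, at least one of them must miss at least half of all overdoses. With one code per event that is true of any two exclusive codes searched on one set of records. The two rows use different records, so it says nothing about the loss in either series here.

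**Conclusion.** The point holds as a minor error in what the table states. Two non-overlapping codes are printed for overdose without explanation, and each, if applied as printed, retrieves only part of the stated outcome. The consequence is clearest for the county count, which lists no second source. For participants it is limited to the medical-record search and may be partly offset by self-report.

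The size of any under-count cannot be derived from the documents. The conclusion rests on two conditions: that the extract follows the printed cells, and that some overdoses are recorded under the code each row leaves out.

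A reader might go further and conclude that both series will certainly under-count, or that comparisons over time are invalid. The documents support neither. The codes may be examples, and a constant code keeps each series consistent with itself.

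**What to change.** Replace both cells with one common opioid-poisoning code set. It should cover at least all of T40.2 and T40.6, and preferably every opioid-poisoning category and intent in the coding manual, confirmed by whoever codes the extract. Apply it at baseline and post-delivery for participants and to every period of the county series. Keep self-report as the second source for participants. If only opioid codes are used, label the county outcome as opioid overdoses, because the present wording is not limited to opioids. If the printed codes were only examples, say so and point to the full list.

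The change affects two table cells and one outcome label. It needs no extra visits or data sources. The downside is a longer code search. The county data are planned for the end of the project, so the correction may come before extraction, but an extract already requested under T40.6 might have to be rerun.
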